**Table 5: Criteria for Potentially Clinically Significant (PCS) Coagulation Parameters**

| Coagulation Parameter                | Flag      | Criteria*      |                      |
|--------------------------------------|-----------|----------------|----------------------|
|                                      |           | Observed Value | Change from Baseline |
| International Normalized ratio (INR) | High (CH) | $> 2.0$        | N/A                  |
|                                      | Low (CL)  | N/A            | N/A                  |

Notes: PCS = potentially clinically significant

CH = high PCS based on criterion value and increase from baseline (if present).]

N/A= Not Applicable

[figure not shown]

\*A post-dose value is considered as a PCS value if it meets both criteria for observed value and change from baseline.

### 20.3 Vital Signs

Descriptive statistics for the mean and mean changes from baseline for the Systolic Blood Pressure, Diastolic blood pressure, Heart rate, Temperature, Respiratory rate, Oxygen Saturation, arterial PH and partial pressure of arterial oxygen at each study visit will be provided.

The number and percentage of subjects with PCS changes in vital signs (systolic and diastolic blood pressure and heart rate) will be presented by treatment group, based on the following thresholds:

**Table 6: Criteria for Potentially Clinically Significant (PCS) Vital Signs**

| Vital Sign Parameter     | Flag | Criteria*      |                             |
|---------------------------------|-------------|-----------------------|-----------------------------|
|                                 |             | Observed Value | Change from Baseline |
| Systolic Blood Pressure (mmHg)  | High (CH)   | $\geq 180$ mmHg       | Increase of $\geq 20$ mmHg  |
|                                 | Low (CL)    | $\leq 90$ mmHg        | Decrease of $\geq 20$ mmHg  |
| Diastolic Blood Pressure (mmHg) | High (CH)   | $\geq 105$ mmHg       | Increase of $\geq 15$ mmHg  |
|                                 | Low (CL)    | $\leq 50$ mmHg        | Decrease of $\geq 15$ mmHg  |
| Heart Rate (bpm)                | High (CH)   | $\geq 120$ bpm        | Increase of $\geq 25\%$     |
|                                 | Low (CL)    | $\leq 50$ bpm         | Decrease of $\geq 25\%$     |
| Respiratory Rate (bpm)          | High (CH)   | $\geq 20$             | N/A                         |
|                                 | Low (CL)    | $\leq 12$             | N/A                         |

Notes: PCS = potentially clinically significant

CH = high PCS based on criterion value and increase from baseline.

CL = low PCS based on criterion value and decrease from baseline.

N/A= Not Applicable

mmHg = Millimeter mercury, bpm = Beat per minute.

\*A post-dose value is considered as a PCS value if it meets both criteria for observed value and change from baseline.

A listing of all vital signs will be provided by subject.

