### Markers for CABP- Clinical Parameters

- PORT Risk Class (II, III/IV)
- Subjects with and without prior systemic antibiotic usage within 72 hours of randomization.
- Subjects with and without presence of SIRS (Systemic Inflammatory Response Syndrome) defined as the presence of at least 2 of: Body temperature >38°C or < 36°C, heart rate > 90 beats/min, respiratory rate > 20 breaths/min, WBC < 4,000 cells/mm^3 or > 12,000 cells/mm^3 or the presence of >10% immature neutrophils

[figure not shown]

(band forms)

- Fever (Yes and No) ( tympanic temperature  $> 38.0^{\circ}\text{C}$  [ $100.4^{\circ}\text{F}$ ] or  $< 36.0^{\circ}\text{C}$  [ $95.5^{\circ}\text{F}$ ])
- Auscultatory findings (Absent/Present)
- Presence of bacteremia at baseline (Yes and No)
- Presence of hypoxia (Yes/No) ( $\text{PaO}_2 < 60$  mmHg or  $\text{O}_2$  saturation  $< 90\%$ )
- Pleural Effusion (No, unilateral, bilateral )
- CABP involvement: Unilateral and Unilobar, Unilateral and multi-lobar, Bilateral

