The coagulation parameters: partial thromboplastin time (PTT), prothrombin time (PT) and International Normalized ratio (INR) was collected using local laboratories but the normal ranges were not obtained. The number and percentage of subjects with PCS changes in the international normalized ratio only will be presented by treatment group, based on the threshold in Table.

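### Section 20.3 and Table 6 disagree on whether respiratory rate enters the PCS count, and the respiratory-rate and INR rows carry no baseline condition although the table notes require one

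*SAP*

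**What the plan says.** SAP Section 18.3 makes the incidence of PCS changes in laboratory parameters, vital signs and ECGs a safety endpoint. Four places bear on this point.

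- **Section 20.3, text.** The count by treatment group covers "PCS changes in vital signs (systolic and diastolic blood pressure and heart rate"). Respiratory rate is named for the mean-change summaries but not for this count.
- **Section 20.3, Table 6.** The table has a fourth parameter, "Respiratory Rate (bpm)", high at ≥20 and low at ≤12, with N/A under change from baseline. The other three parameters pair a limit with a change: 20 mmHg systolic, 15 mmHg diastolic, 25% for heart rate. The notes define the high flag as "CH = high PCS based on criterion value and increase from baseline", with a matching definition for the low flag. The footnote adds: "A post-dose value is considered as a PCS value if it meets both criteria for observed value and change from baseline".
- **Section 20.2, text before Table 5.** "The number and percentage of subjects with PCS changes in the international normalized ratio only will be presented by treatment group". The same paragraph says that normal ranges for the coagulation tests were not obtained.
- **Section 20.2, Table 5.** The only row is "International Normalized ratio (INR)", high above 2.0, change N/A. The note reads "CH = high PCS based on criterion value and increase from baseline (if present)", but the footnote under the table repeats the requirement that both criteria be met.

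**The concern.** Two things are unsettled. First, a programmer cannot tell whether a respiratory-rate count is to be produced: the sentence that orders the count leaves it out, and the table it introduces puts it in. Second, if the count is produced, the N/A cell leaves only the observed value to apply, against the table's own notes.

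The second matters because every subject has pneumonia. The SIRS subgroup definition in Section 19.4 lists "respiratory rate > 20 breaths/min" among its components, so the SAP recognises a raised rate as a possible feature of the illness at entry. A limit of ≥20 without a baseline condition can flag subjects for the disease they came in with. Randomisation balances that background between the arms but does not remove it. It raises both rates and dilutes any real difference in new abnormalities.

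For INR the mechanism is the same. Without normal ranges, the shift tables planned in Section 20.2 cannot show who was already raised.

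**Working it through.** **1. How the rows are built.**

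| Place | Parameter | Observed limit | Baseline condition |
|---|---|---|---|
| Tables 3–4 | all applicable rows | multiple of ULN or LLN | % change |
| Table 5 | INR | >2.0 | N/A |
| Table 6 | systolic and diastolic pressure, heart rate | fixed limits | stated change |
| Table 6 | respiratory rate | ≥20, ≤12 | N/A |
| Table 7 | ECG | mostly fixed limits | a baseline cut-off or a change |

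INR and respiratory rate are the only parameters with an observed limit and no baseline condition.

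**2. One subject through the rule.** Take a rate of 28 at baseline and 22 after dosing.
- As printed: 22 ≥ 20, so flagged high.
- With a baseline cut-off: 28 is not below 20, so not flagged.
- With the 25% increase that Table 6 uses for heart rate: (22 − 28)/28 = −21%, so not flagged.

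**3. Size, illustrative only.** The SAP states no respiratory-rate figure to reproduce. Section 8 schedules vital signs at five visits after Day 1 (Days 2, 3, 4, EOT, TOC). Both models below are simulations of 200,000 subjects with readings rounded to whole numbers and no drug effect. All distributions are assumptions.

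*Model A: stable rate.* One baseline and five later readings from the same normal distribution, within-subject correlation 0.3 to 0.6 (this gives the ranges). Flag = any later reading ≥20 or ≤12.

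| Mean, SD | Flagged | Of these, beyond a limit at baseline | Flagged with baseline cut-off |
|---|---|---|---|
| 18, 2 | 50–62% | 29–40% | 30–44% |
| 18, 3 | 70–81% | 37–43% | 40–54% |
| 19, 2 | 71–82% | 45–53% | 34–46% |
| 19, 3 | 79–88% | 48–53% | 37–48% |
| 20, 2 | 87–94% | 62–67% | 29–36% |
| 20, 3 | 87–94% | 59–63% | 32–40% |

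*Model B: raised baseline with recovery.* Between-subject SD 2.5, visit-to-visit SD 1.5, total fall of 0, 3 or 6 per minute by TOC (this gives the ranges). High limit only.

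| Baseline mean | Flagged | Of these, ≥20 at baseline | With baseline <20 | With ≥25% increase |
|---|---|---|---|---|
| 18 | 21.1–53.5% | 52.1–76.4% | 5.0–25.6% | 0.4–6.1% |
| 20 | 46.4–79.7% | 69.2–85.8% | 6.6–24.6% | 0.5–6.3% |
| 22 | 73.5–94.4% | 84.6–93.0% | 5.2–14.6% | 0.4–5.1% |
| 24 | 91.2–99.0% | 94.7–97.3% | 2.5–5.2% | 0.3–3.5% |

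Over both models, the share of flagged subjects already abnormal at baseline runs from about 29% to 97%. In Model A much of the flagging comes from a limit close to the assumed mean, not from carry-over, and a baseline cut-off leaves 29–54% flagged. In Model B carry-over dominates and the cut-off removes most flags.

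**4. INR.** The SAP gives no INR distribution, so nothing can be computed. Only subjects above 2.0 before the first dose can be miscounted.

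**The case against.** The strongest reply is that the sentence ordering the vital-sign count omits respiratory rate. If that sentence governs, no such count is produced and the Table 6 row is merely unused. This stands. The certain defect in the vital-sign section is the contradiction; the miscounting is conditional on the table governing.

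For INR, the words in brackets in the Table 5 note show that the threshold-only rule was intended. This stands as to intent, but the footnote under the same table still asks for both criteria and the text still calls the results changes. Whether anyone enters above 2.0 depends on eligibility rules not shown here.

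Other summaries carry baseline information: mean changes for respiratory rate (Section 20.3) and coagulation tests (Section 20.2), and by-subject listings. They let a reader look up baseline status but do not correct the counts. The counts are also descriptive, with no planned test.

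Three stronger readings are tempting and not supported:
- *The row will be near saturation in both arms.* The SAP gives no distribution, and Model B goes as low as 21%.
- *The SIRS component shows that most subjects enter with a raised rate.* It is one of several components, at least two are needed, and subjects are split into those with and without SIRS.
- *Table 7 pairs every ECG limit with a baseline cut-off.* ECG heart rate uses a 25% change, one QTcF row pairs >500 with an increase above 60, and two QTcF rows have no observed limit.

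**Conclusion.** The point holds as a minor inconsistency. Section 20.3 contradicts Table 6 on which vital signs are counted. The respiratory-rate row contradicts the notes and footnote of its own table, and the INR row contradicts the footnote of Table 5. If Table 6 is followed as printed, persisting baseline abnormalities are reported as on-treatment changes.

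A reader might infer that the SAP definitely reports respiratory rate this way, or that one arm is favoured. Neither follows: the text leaves the count open, and the rule applies equally to both randomised arms. The expected effect is inflated and diluted rates.

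The size rests wholly on assumed distributions: about 50–88% flagged at a stable mean of 18–19, 87–94% at 20, and 21–99% under a recovery model. The INR effect is probably small and cannot be quantified. The primary efficacy analysis is untouched.

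**What to change.** 1. Make the text of Section 20.3 and Table 6 list the same parameters.
2. For INR, and for respiratory rate if it is kept, do one of two things. Either count a flag only when baseline was not already beyond the same limit or a stated change is met, as the other PCS tables do with a change or a baseline cut-off. Or label these rows as observed post-baseline values and tabulate them by baseline status.
3. Align the notes and the both-criteria footnotes of Tables 5 and 6 with any row left as N/A.

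The cost is a few table cells, one sentence and the notes. Section 8 already schedules vital signs and coagulation tests at Screening, so no new data are needed.

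There are two downsides. With a baseline cut-off alone, subjects abnormal at entry who worsen further appear only in the mean changes and listings, unless a change criterion is added. And if the limit lies close to the usual rate in this population, a cut-off alone will still flag many subjects; tabulating by baseline status would make that visible.

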### 20.4 Electrocardiogram (ECG)

The number and percentage of subjects with PCS changes in ECG will be presented by treatment group, based on the thresholds given below. Summaries of the number and

[figure not shown]

percentage (%) of subjects meeting PCS criteria will be generated using the subgroups of subjects in the safety analyses set that have both a baseline and any post-baseline ECG evaluation.

**Table 7.Criteria for Potentially Clinically Significant Safety ECG Values.**

| ECG Parameter                                                                                                                                                                                                                                                                                                                                                                                                                                                                       | Flag      | PCS Criteria a |                                                |
|-------------------------------------------------------------------------------------------------------------------------------------------------------------------------------------------------------------------------------------------------------------------------------------------------------------------------------------------------------------------------------------------------------------------------------------------------------------------------------------|-----------|---------------------------|------------------------------------------------|
|                                                                                                                                                                                                                                                                                                                                                                                                                                                                                     |           | Criterion Value           | Change from baseline or baseline Cut-off Value |
| Heart Rate (bpm)                                                                                                                                                                                                                                                                                                                                                                                                                                                                    | High (CH) | >120                      | Increase of $\geq 25\%$                        |
|                                                                                                                                                                                                                                                                                                                                                                                                                                                                                     | Low (CL)  | <50                       | Decrease of $\geq 25\%$                        |
| PR Interval (ms)                                                                                                                                                                                                                                                                                                                                                                                                                                                                    | High (CH) | >200                      | Baseline $\leq 200$ msec                       |
|                                                                                                                                                                                                                                                                                                                                                                                                                                                                                     | Low (CL)  | < 120                     | Baseline $\geq 120$ msec                       |
| QRS Interval (ms)                                                                                                                                                                                                                                                                                                                                                                                                                                                                   | High (CH) | >100                      | Baseline $\leq 100$                            |
| QT Interval (ms)                                                                                                                                                                                                                                                                                                                                                                                                                                                                    | High (CH) | >500                      | Baseline $\leq 500$ msec                       |
| QT Interval (ms)                                                                                                                                                                                                                                                                                                                                                                                                                                                                    | High (CH) | >470                      | Baseline $\leq 470$ msec                       |
| QTcF (ms)                                                                                                                                                                                                                                                                                                                                                                                                                                                                           | High (CH) | >500                      | Baseline of $\leq 500$ msec                    |
| QTcF (ms)                                                                                                                                                                                                                                                                                                                                                                                                                                                                           | High (CH) | >500                      | Increase from baseline >60                     |
| QTcF (ms)                                                                                                                                                                                                                                                                                                                                                                                                                                                                           | High (CH) | >480                      | Baseline $\leq 480$ msec                       |
| QTcF (ms)                                                                                                                                                                                                                                                                                                                                                                                                                                                                           | High (CH) |                           | Increase from baseline >30                     |
| QTcF (ms)                                                                                                                                                                                                                                                                                                                                                                                                                                                                           | High (CH) |                           | Increase from baseline >60                     |
| QTcB (ms)                                                                                                                                                                                                                                                                                                                                                                                                                                                                           | High (CH) | >500                      | Baseline $\leq 500$ msec                       |
| 
Notes: CH = high PCS based on criterion value and increase from baseline (or baseline cut off value).
 CL = low PCS based on criterion value and decrease from baseline.
 PCS = potentially clinically significant. bpm = Beat per minute. msec = Millisecond.
 QTcF (based on RR i.e. <math>QTcF = QT/(RR)^{1/3}</math>)
 aA post-dose value is considered as a PCS value if it meets both criteria for observed value and change from baseline.
 |           |                           |                                                |

All ECG measurements and the overall interpretation will be listed by subject.

[figure not shown]

**21. PK ANALYSIS**

All PK related summaries will be done separately and reported in the PK report.

[figure not shown]

**22. MULTIPLE COMPARISONS**

No multiple comparison adjustment shall be made in this study.

[figure not shown]

## 23. METHODS FOR HANDLING MISSING DATA

- For demographic and baseline characteristics, each variable shall be presented using all available data. Subjects with missing data shall be excluded only from analyses sets for which data are not available

- Handling of Missing/Partial Dates for Adverse Events:

### Partial/Missing Start Date

Missing day - Impute the 1st of the month unless month is same as month of first dose of study drug then impute first dose date.

Missing day and month – Impute 1st January unless year is the same as first dose date then impute first dose date.

